#### Analysis: Secondary End Points

In accordance with the scoring rules of the OPTION grid, an OPTION score will be calculated for each patient-health care professional dyad if 100% of the 5 OPTION grid items have been completed. A total score between 0 and 20 will then be obtained by summing the answers to the 5 OPTION grid items between 0 and 4. The total score will be converted between 0 and 100, with high values indicating exemplary behavior by the dyad in adopting SDM. The OPTION score will be expressed as the mean and standard deviation for each group and will be compared using the Wilcoxon test.

In accordance with the scoring rules of the SURE questionnaire, a SURE score will be calculated for each patient if 100% of the 4 questionnaire items have been completed. A total score between 0 and 4 (a high value indicates a decisional conflict) will then be obtained by summing the binary responses of the 4 questionnaire items. The SURE score will be expressed as the mean and standard deviation for each group and will be compared using the Wilcoxon test. The percentage of patients whose SURE score is less than or equal to 3 (indicating a decisional conflict) will also be calculated in each group and compared using the chi-square test.

In accordance with the scoring rules of the CollaboRATE questionnaire, a CollaboRATE score will be calculated for each patient if 100% of the 3 questionnaire items have been completed. A total score between 0 and 9 (high values indicating a high level of SDM) will then be obtained by averaging the answers to the 3 questions between 0 and 9 on the questionnaire. The CollaboRATE score will be expressed as the mean and standard deviation for each group and will be compared using the Wilcoxon test.

A Spielberger State-Trait Anxiety Inventory score will be calculated for each patient if 100% of the 20 questionnaire items have been completed. A total score between 20 and 80 (high values indicating a high level of anxiety) will then be obtained by summing the scores associated with the 20 items. For questions 3, 4, 6, 7, 9, 12, 13, 14, 17, and 18, 1 point is awarded for not at all, 2 points for somewhat, 3 points for moderately, and 4 points for very much. For questions 1, 2, 5, 8, 10, 11, 15, 16, 19, and 20, the scoring will be reversed, that is, 4 points for not at all, 3 points for a little, 2 points for moderately, and 1 point for a lot. The Spielberger State-Trait Anxiety Inventory score will be expressed as the mean and standard deviation for each group and will be compared using the Wilcoxon test.

Semistructured individual interviews designed to assess the experience of information and decision-making procedures in the control and intervention groups and the effects of SDM on patients’ and health care professionals’ experience of care in the intervention groups only will be analyzed by means of a thematic content analysis conducted using NVivo 10 (QSR International) and 2 researchers participating in the study based on the interview guide developed and previously tested with patients at the CFRC in Lyon. The focus groups conducted in the control and intervention groups designed to analyze the individual and organizational factors influencing the implementation or nonimplementation of SDM will be transcribed on the basis of notes taken during the focus groups and will be analyzed on the basis of the interview guide developed.

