### Outcomes and Measures

The outcomes are measured using the following measures.

Adoption or nonadoption of SDM: SDM-Q-9 [34,35], CollaboRATE questionnaire [36], OPTION (Observing Patient Involvement in Shared Decision Making) questionnaire [37,38]Level of patient knowledge: knowledge questionnaire developed by the authors on the basis of their previous work [39] and the literature since no validated knowledge questionnaire existsPatient anxiety level: Spielberger State-Trait Anxiety Inventory [40]Patients’ level of decisional conflict: SURE questionnaire [41]Patients’ experience of information and decision-making procedures and more specifically of SDM implementationIndividual and organizational factors influencing SDM implementation

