## Results

Forty patients will be included (8 patients in each center), that is, 60 consultation observations (2 consultations per patient in the intervention groups given the modalities of the SDM process) will be conducted in 2025. Eight focus groups will be conducted in the 5 centers (2 groups in each intervention CFRC and 1 group in each control CFRC) in 2025. This qualitative corpus plus responses to the patient and physician questionnaires will make it possible to know whether the practice of SDM in CFRCs is increased by an implementation strategy and to analyze the experience of patients and their relatives regarding decision-making modalities. Analysis of the outcomes and experience of the implementation of SDM are of importance to identify the facilitators and barriers to SDM from patients’ and CFRCs’ point of view.

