## Abbreviations

CFRC: cystic fibrosis reference center
FREeDOM: French collaboration on shared decision-making
MAGIC: Making Good Decisions in Collaboration
OPTION: Observing Patient Involvement in Shared Decision Making
SDM: shared decision-making
SDM-Q-9: 9-item Shared Decision-Making Questionnaire
StaRi: Standards for Reporting Implementation Studies
SURE: Sure of myself, Understand information, Risk-benefit ratio, Encouragement

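### The SURE decisional-conflict score is given two opposite directions in one paragraph, and the plan does not say which answer scores 1

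*Protocol article*

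**What the plan says.** All the scoring text is in one paragraph of the Protocol article, under Analysis: Secondary End Points.

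- Completeness: "a SURE score will be calculated for each patient if 100% of the 4 questionnaire items have been completed".
- Direction: "A total score between 0 and 4 (a high value indicates a decisional conflict) will then be obtained by summing the binary responses".
- Score analysis: "The SURE score will be expressed as the mean and standard deviation for each group and will be compared using the Wilcoxon test".
- Dichotomy: "The percentage of patients whose SURE score is less than or equal to 3 (indicating a decisional conflict) will also be calculated in each group", with a chi-square comparison between groups.

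The paragraph opens by appealing to the questionnaire's own scoring rules, but it does not say which of the two answers to an item counts as 1.

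Elsewhere, Outcomes and Measures names SURE as the measure for this end point: "Patients’ level of decisional conflict: SURE questionnaire". The visit descriptions and the list of objectives only name the questionnaire. The Abbreviations section expands the acronym: "SURE: Sure of myself, Understand information, Risk-benefit ratio, Encouragement". The direction is settled nowhere else.

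**The concern.** Under the first statement, a total of 4 is the greatest conflict. Under the second, 4 is the only total without conflict. A programmer has to disregard one of the two, and a reader of the results cannot tell which was disregarded.

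Decisional conflict is a stated secondary objective and a listed secondary end point, and SURE is the only questionnaire named for it. At stake is whether a group difference is reported with the right sign and whether the percentage with conflict means anything. If the direction is settled only once results are visible, the sign also becomes open to a choice made after the fact.

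The article gives one consistent direction for SDM-Q-9, OPTION, CollaboRATE and the anxiety inventory, and item-level coding for the last. Among these scores, only SURE has two.

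**Working it through.** **Inputs.** From the article: four binary items, all required; total 0 to 4; the stated direction; the cut-off at 3 or less; 40 patients, 8 per center, so 3 × 8 = 24 intervention and 2 × 8 = 16 control. Assumed, because the article gives no SURE response rates: q, the probability that a patient answers an item in the 'unsure' direction. There is no figure in the plan to reproduce.

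**Step 1: can both statements hold?** If higher totals mean more conflict and a total of 3 counts as conflict, then 4 must count as conflict too. The cut-off excludes 4. The statements are incompatible whatever the coding.

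**Step 2: what each coding does.** Four binary items give 2^4 = 16 answer patterns. Let U be the number of unsure answers.

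| | 'Sure' = 1 (total = 4 − U) | 'Unsure' = 1 (total = U) |
|---|---|---|
| Agrees with the direction statement | no | yes |
| Patterns with total of 3 or less | 15 of 16 | 15 of 16 |
| The one pattern not flagged | fully sure (U = 0) | fully unsure (U = 4) |
| Cut-off coherent | yes | no |

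The classifications differ for two patterns only: fully sure and fully unsure. The fully sure pattern may be common, so the effect can be large.

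**Step 3: 'unsure' = 1, independent items.** Share with any unsure item = 1 − (1 − q)^4. Share flagged by the cut-off = 1 − q^4.

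| q | Any unsure item | Flagged |
|---|---|---|
| 0.1 | 1 − 0.6561 = 34.4% | 1 − 0.0001 = 99.99% |
| 0.2 | 1 − 0.4096 = 59.0% | 1 − 0.0016 = 99.8% |
| 0.3 | 1 − 0.2401 = 76.0% | 1 − 0.0081 = 99.2% |
| 0.5 | 1 − 0.0625 = 93.8% | 1 − 0.0625 = 93.8% |
| 0.7 | 1 − 0.0081 = 99.2% | 1 − 0.2401 = 76.0% |

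**Step 4: correlated items.** The items address one construct, so independence is doubtful. With a beta-binomial model, q from 0.1 to 0.3 and intra-patient correlation 0.3 or 0.6, the share flagged is 84% to 99%, against 17% to 60% with any unsure item.

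**Step 5: effect on a group contrast.** Take q = 0.1 in the intervention group and 0.3 in the control group, with independent items. The share with any unsure item differs by 34.4% − 76.0% = −41.6 percentage points. Under 'unsure' = 1 the flagged share differs by 99.99% − 99.19% = +0.8 points: the contrast almost vanishes and its sign flips.

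**Step 6: 'sure' = 1 and the score analysis.** Reversing the scale replaces each total t by 4 − t. In one simulated example with the q values of Step 5 (24 and 16 patients), mean unsure counts were 0.42 and 1.25, so mean 'sure' totals were 4 − 0.42 = 3.58 and 4 − 1.25 = 2.75. The two-sided Wilcoxon p-value was 0.0056 on both scales. If 3.58 against 2.75 is read with the article's parenthesis, the group with fewer unsure answers appears to have more conflict.

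**The case against.** The strongest reply is that the paragraph defers to the instrument's scoring rules. Those would probably settle the coding when the items are scored, leaving one wrong parenthesis. Each branch also damages only one of the two SURE analyses, and because the score requires all four items, the total can be rescored from the item responses.

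Much of this stands. A reader might infer that the result *will* be inverted or *will* class nearly every patient as conflicted. The document does not support that: it is a risk that depends on which statement is followed, and the near-universal flagging rests on assumed response rates. The reply does not remove the contradiction, since the paragraph that invokes the rules then states two opposite ones.

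A reader might also take the coding 'yes = 1' as established. It is the likelier reading, because it fits the cut-off and the positively named items, but the acronym lists topics, not item wording or scores.

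Finally, a reader might infer that the chi-square test is unsuitable for 24 against 16 patients. That depends on an unknown rate: the smallest expected cell is 16 × 0.344 = 5.5 at 34% conflicted, 16 × 0.41 = 6.6 at 59%, and 16 × 0.24 = 3.8 at 76%. A fallback for sparse cells is commonly left to the analysis plan, which is not shown, so it is no part of this point.

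**Conclusion.** The concern holds as an internal contradiction in a stated scoring rule. It follows from the text alone and needs no assumption.

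Its consequence is conditional. With 'sure' = 1, the percentage is sound; only the interpretation of the means and of the Wilcoxon direction is at risk, not the computed difference or the p-value. With 'unsure' = 1, the percentage loses its meaning. The size of that loss rests on assumed item rates: about 99% or more flagged for q from 0.1 to 0.3 with independent items, 84% to 99% with correlated items, and 76% at q = 0.7.

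The scope is one secondary end point in a 40-patient pilot. The primary SDM-Q-9 analysis is untouched.

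**What to change.** Check the instrument's scoring rules, state which answer scores 1, and make the direction and the cut-off agree. Two forms are coherent:

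- **Likelier, given the cut-off and the item names:** 'sure' answer = 1; higher total = less decisional conflict; conflict = total of 3 or less. The parenthesis linking a high value to conflict is deleted.
- **Alternative:** 'unsure' answer = 1; higher total = more decisional conflict; conflict = total of 1 or more.

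Both flag the same 15 of 16 answer patterns, so the percentage with conflict is the same under either.

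The cost is about one sentence of protocol or analysis-plan wording, with no change to data collection. It should be settled before the SURE data are analyzed.

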### Design and Setting of the Study

Based on our previous work on SDM in cystic fibrosis [21] and the Consolidated Framework for Implementation Research of Damschroder et al [32], this quasi-experimental here-elsewhere study compares the populations of 3 centers receiving the intervention with those of 2 centers not receiving it (controls). The 5 centers will be studied simultaneously to reduce the risk of contamination of the control group. The evaluation will follow a mixed methods approach, combining qualitative methods (consultations observations, individual semistructured interviews with patients, and focus groups with health care professionals) with quantitative methods (self-administered questionnaires). A convergent mixed methods approach will be used, with concomitant data collection, separate analysis, and subsequent linking of results. This study conforms to the StaRi (Standards for Reporting Implementation Studies) checklist (Multimedia Appendix 1).

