### Data Collection and Analysis

#### Sample Size

As this is a pilot study, 40 patients will be included and interviewed over a 12-month period. The number of patients included corresponds to the active patient file of the 5 CFRCs over the 12-month inclusion period. Five physicians (1 in each center) will be involved in this study.

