#### Analysis

All patients and health care professionals included in this study are in accordance with the inclusion and noninclusion criteria. The primary end point is the adoption or nonadoption of SDM from the patient’s and health care professional’s point of view. The secondary end points are patient knowledge; patient anxiety levels; patients’ level of decisional conflict; patients’ experience of information and decision-making procedures, and more specifically of SDM implementation; effect of SDM on the physician; and individual and organizational factors influencing SDM implementation.

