#### Analysis: Primary End Point

Adoption of SDM as perceived by the patient and measured using SDM-Q-9 will be analyzed in patients with no missing data on this criterion, although an approach to managing missing data may be considered. The frequency distribution of the 6 modalities of SDM-Q-9 will be described for each group in the patient unit. A total score will be obtained by summing the scores for each of the 9 questions. A transformation will be applied to obtain a total score between 0 and 100, with 0 indicating nonadoption of SDM as perceived by the patient and conversely 100 indicating adoption of SDM as perceived by the patient. The total score will be described in each group by mean, standard deviation, median, quartiles, and range, and will be compared between the 2 groups with a nonparametric Wilcoxon test. For patients in the intervention group, the variation in the responses to each of the SDM-Q-9 questions between the 2 consultations will be tested using the McNemar test (test adapted to paired data). Total SDM-Q-9 scores between the 2 consultations will be compared using the Wilcoxon signed-rank test. The same analysis will be performed on the health care professional unit to compare the adoption of SDM as perceived by the health care professional. Discordances between patient and health care professional responses to each of the 9 questions on SDM-Q-9 will be described and tested using the McNemar test. The total SDM-Q-9 score obtained on the patient unit and the professional unit will be compared using the Wilcoxon signed-rank test.

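### The STAI anxiety score needs all 20 items with no fallback, so one blank item removes a patient from this secondary comparison

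*Protocol article*

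**What the plan says.** Patient anxiety is a secondary end point (Protocol article, Analysis: "The secondary end points are patient knowledge; patient anxiety levels; patients’ level of decisional conflict"). It is measured with the 20-item STAI, each item scored 1 to 4 with ten items reversed, giving a total from 20 to 80 that is compared between groups with a Wilcoxon test. Under Analysis: Secondary End Points, the STAI "score will be calculated for each patient if 100% of the 20 questionnaire items have been completed". Nothing is said about a form with one or two blanks.

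The same section applies an all-items condition to OPTION (5 items), SURE (4) and CollaboRATE (3). For those three the article ties the scoring to the instrument's own rules; the STAI sentence makes no such reference.

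On size, the Results section says "Forty patients will be included (8 patients in each center"), and the design "compares the populations of 3 centers receiving the intervention with those of 2 centers not receiving it (controls"). Under Visit V1 and Decision-Making Visit (V2), the methodologist is to see that the patient completes the questionnaires, STAI included.

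**The concern.** The rule is stated, so an analysis that follows the article will apply it. An all-items condition bites harder the longer the scale, and STAI is four times as long as the next longest instrument under that condition (20 items against 5). A form with 19 answers holds nearly all the information on that patient's anxiety, yet it is treated like a form never returned.

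Lost scores would be hard to replace. The Sample Size section ties the 40 patients to the active patient file of the five centers over 12 months, and the Discussion warns that few patients are eligible. The cost is precision in a small comparison. If skipping an item were related to anxiety, dropping those patients could also shift the group difference, but the article gives no information on whether that happens.

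**Working it through.** **Inputs from the article.** Patients: 5 centers × 8 = 40, which reproduces the stated total. Groups: 3 × 8 = 24 intervention and 2 × 8 = 16 control. STAI items: 20. The article states no blank rate, significance level, power or effect size, so there is no power figure to reproduce.

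**Assumed.** Each item is blank with probability p, independently, with p from 0.1% to 2%. For precision: two-sided 5% level, 80% power, normal approximation, clustering by center ignored.

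**Loss under the all-items rule.** Expected loss = 40 × (1 − (1 − p)^20). For example, at p = 1%: 0.99^20 = 0.818, so 40 × 0.182 = 7.3.

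**Loss with up to 2 blanks allowed.** Expected scores kept = 40 × P(X ≤ 2), where X is binomial (20, p).

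**Smallest detectable difference in SD units.** (1.960 + 0.842) × √(1/n₁ + 1/n₂). With 24 v 16: 2.802 × 0.323 = 0.90.

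| p per item | Share of complete forms | Scores lost of 40, all-items rule | Detectable difference (SD) | Scores kept if ≤ 2 blanks allowed |
|---|---|---|---|---|
| 0 | 1.000 | 0 | 0.90 | 40 |
| 0.1% | 0.980 | 0.8 | 0.91 | 40.0 |
| 0.5% | 0.905 | 3.8 | 0.95 | 39.99 |
| 1% | 0.818 | 7.3 | 1.00 | 39.96 |
| 2% | 0.668 | 13.3 | 1.11 | 39.72 |

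At 2%, the groups shrink to about 24 × 0.668 = 16.0 and 16 × 0.668 = 10.7.

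**If blanks cluster.** What matters then is the share of patients with any blank. At 5%, 10% or 20% of patients, 38, 36 or 32 scores remain, and the detectable difference is 0.93, 0.95 or 1.01 SD.

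**How far proration can err.** After reversal an item lies between 1 and 4, so replacing a blank by the patient's own item mean is wrong by at most 3 points. With two blanks the error is at most 6 points on a scale of width 80 − 20 = 60. The prorated total stays between 20 × 1 = 20 and 20 × 4 = 80.

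**The case against.** The best defense is supervised completion. The methodologist has a duty at both visits to see that the forms are filled in, reads them aloud where needed, and normally interviews the patient straight after the consultation. A member of the center may hand out the forms, and the methodologist's attendance may be by videoconference, but the duty still applies. Blank rates near the bottom of the table are therefore plausible, and at 0.1% less than one score is lost. Independence also overstates the loss if a few patients leave several blanks. These points stand, and they make the size uncertain.

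Complete-item scoring is also prespecified, reproducible and consistent across four instruments. That the STAI sentence does not refer to scoring rules does not show that the instrument allows proration. This stands too, and is why the remedy needs a check against those rules. Nor would proration cure bias if patients skip the items that trouble them most.

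The study is a pilot ("As this is a pilot study, 40 patients will be included and interviewed over a 12-month period"), with no power target to miss, and STAI is secondary.

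A reader might infer that the primary SDM-Q-9 analysis has the same fault, since the score "will be analyzed in patients with no missing data on this criterion". The document does not support that reading. The same sentence goes on, "although an approach to managing missing data may be considered", and the section sets no item-level condition; it says only, "A total score will be obtained by summing the scores for each of the 9 questions". What the other approach would be is detail commonly left to the statistical analysis plan, which is not shown.

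**Conclusion.** The point holds for STAI alone, as an inexpensive improvement to a secondary end point. The rule is explicit, has no fallback, and turns a single blank into a lost patient.

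How many patients that means is unknown. The range of about 0.8 to 13.3 of 40 scores rests wholly on assumed rates of 0.1% to 2% per item and on independence. A reader might take the upper end, roughly 16 v 11 patients, as the expected outcome, or conclude that the plan wastes patients. Neither follows: the upper end belongs only to the 2% case, and the article arranges for completion to be checked. The primary comparison is not affected by this rule.

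**What to change.** Prespecify that the STAI score is calculated when at most 2 of the 20 items are blank, as the mean of the answered items (after reversal) multiplied by 20. Confirm first that the instrument's scoring rules allow this. The limit of 2 is a proposal and does not come from the article. Report the number of forms with 0, 1, 2 and more blanks by group, and repeat the comparison with complete forms only as a sensitivity analysis.

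The cost is a sentence in the analysis plan and a line of scoring code, settled before the data are seen. The price is the assumption that a blank item resembles the patient's other answers. If blanks turn out to be rare, the two analyses will nearly coincide. The same kind of item-level rule could be written for SDM-Q-9 when the approach to its missing data is specified.
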